## Abstract

**Introduction:**

In settings where the private sector constitutes a larger part of the health system, profit-gathering can take primacy over patients’ well-being. In their interactions with pharmaceutical companies, private general practitioners (GPs) can experience the conflict of interest (COI), a situation whereby the impartiality of GPs’ professional decision making may be influenced by secondary interests such as financial gains from prescribing specific pharmaceutical brands.

**Methods and analysis:**

This study is a randomised controlled trial to assess the impact of a multifaceted intervention on GPs’ medical practice. The study sample consists of 419 registered GPs who own/work in private clinics and will be randomly assigned to intervention and control groups. The intervention group GPs will be exposed to emotive and educational seminars on medical ethics, whereas control group GPs will be given seminars on general medical topics. The primary outcome measure will be GPs’ prescribing practices, whereas the secondary outcome measures will be their knowledge and attitudes regarding COI that arises from pharmaceutical incentivisation. In addition to a novel standardised pharmaceutical representatives (SPSR) method, in which field researchers will simulate pharmaceutical marketing with GPs, presurvey and postsurvey, and qualitative interviewing will be performed to collect data on GPs’ knowledge, attitudes and practices in relation to COI linked with pharmaceutical incentives. Univariate and multivariate statistical analyses will be performed to measure a change in GPs’ knowledge, attitudes and practices, while qualitative analysis will add to our understanding of the quantitative SPSR data.

**Ethics and dissemination:**

Ethics approval has been obtained from the Pakistan National Bioethics Committee (# 4-87/NBC-582/21/1364), the Aga Khan University (# 2020-4759-1129) and the London School of Hygiene and Tropical Medicine (# 26506). We will release results within 6–9 months of the study’s completion.

**Trial registration number:**

ISRCTN12294839.

STRENGTHS AND LIMITATIONS OF THIS STUDYThe study assesses whether emotive sensitisation can help reduce profit-led prescribing.It evaluates the potential usability of the standardised pharmaceutical representatives method to ensure quality control.It uses a mixed-method approach to perform a comprehensive assessment.The inclusion of more female general practitioners would have provided additional insights.

## Introduction

The pharmaceutical industry is often a vital source of information for general practitioners (GPs) to learn about pharmaceutical products. This information helps GPs make informed choices and decisions in relation to patients’ diverse health needs.^1^ Nevertheless, the relationship between the pharmaceutical industry and GPs can negatively affect patients’ health and well-being, if/when incentives are mobilised to maximise profits through inappropriate prescribing.^2^ As a result of pharmaceutical incentivisation, GPs may experience a conflict of interest (COI)—a situation where GPs’ professional judgement is influenced by a secondary interest, such as financial gain, leading to a decision that conflicts with their interpretation of the patient’s best interest.^3^ There is evidence that GPs who engage in pharmaceutical incentivisation are likely to prescribe unnecessary and/or more expensive medicines to patients, further contributing to an increased financial burden on them.^4 5^ In addition, pharmaceutical incentivisation has important implications for antimicrobial resistance, as to achieve pharmaceutical targets, GPs may prescribe antibiotics to patients with common self-resolving ailments like cold and influenza.^6^

In Pakistan, the health system is composed of public and private sectors where a large proportion of patients access healthcare from private GPs.^7^ At the same time, the country is home to over 600 pharmaceutical companies including multinational, national and franchise-based local companies.^8^ To compete in the market, pharmaceutical companies use incentivisation as a major tool to maximise profits from GPs’ prescriptions.^9^ On the other hand, in Pakistan, poverty represents one of the key problems that people and the inextricable link between poverty and a lack of education and health awareness gives perfect grounds to the pharmaceutical industry and GPs to capitalise on patients’ weaknesses to maximise profits from pharmaceutical products, further exacerbating problems for patients.^10 11^

Our previous research in Pakistan helped us identify three interlinked health system constraints that shape private GPs’ decisions on receiving personal benefits from prescribing antibiotics.^12–16^ First, insufficient income generation from patient consultations alone—as patients are unwilling to spend substantial sums on medical advice without a prescription—resulted in a reliance on other sources of income.^15^ Second, limited opportunities for continuing medical education (CME) other than from pharmaceutical companies may lead to a close relationship with pharmaceutical sales representatives (PSRs).^13^ Third, inadequate access to diagnostic tools to establish the clinical need for antibiotics, making it easier for doctors to justify defensive overprescribing.^13^ We also found that private doctors engage in activities such as generating extra income from receiving monetary or non-monetary incentives, and sponsorships to attend academic events from pharmaceutical companies in return for meeting sales targets for specific medicines.^13^ These behaviours of private physicians stem from deeply embedded dynamics of pluralistic health systems. Hence, not only did these studies provide rich insights into critical health system and policy dynamics, but also helped to identify the issue of COI in medical practice and how this contributes to unnecessary prescribing of medicines in primary care settings.

Therefore, to improve the quality of primary care, actions are required that address pharmaceutical incentivisation.^17 18^ However, major impediments to progress on this front include limited assessment of interventions for improving the quality of care delivered by private GPs,^19 20^ and a marked absence of attention by researchers and policy makers as to the role of political, social, economic and cultural factors that influence the effectiveness and scalability of interventions.^21^ Furthermore, prohibiting or constraining private physicians through the enforcement of regulations may fail because of a lack of political and social support and enforcement capacity, as well as insufficient public sector capacity to provide care.^19^ Training interventions focusing on increasing technical knowledge and skills are the most common approach used to improve the quality of care.^22 23^ Our previous research also suggests that an intervention that can enhance GPs’ understanding of COI in medical practice might be useful to enable them to recognise potential actions that threaten professional ethics in their medical practice while interacting with PSRs.^13 15^ It is clear, however, from consistent evidence on the ‘know-do’ gap that COI related to profit generation from medicine sales plays a critical role in prescribing decisions, as do values associated with professional ethics and altruism.^24 25^ To improve GPs’ understanding of COI in medical practice, we aim to develop an intervention based on emotive and educational seminars and to test their impact on private GPs’ knowledge, attitudes and practices in relation to professional ethics in medical practice.

### Study objectives

The overarching aim of our study is to assess the impact of a multifaceted intervention for improving GPs’ prescribing practices in relation to COI linked with pharmaceutical incentivisation. The specific objectives of the study are to:

Alter GPs’ prescribing practice in response to pharmaceutical incentives.Improve their knowledge of professional ethics in medical practice.Shift their attitudes to give primacy to patients’ well-being rather than pharmaceutical incentives.

## Methods

We plan to complete the study in three phases: formative, intervention and evaluation. The study is being undertaken in Karachi, which is the largest city by geographical area and population size in Pakistan.^26^ In 2021, we completed the formative phase of the study, whereas the intervention and evaluation phases will be completed in 2022.

### Formative work

We used semistructured interviews to obtain information from GPs, policy actors and PSRs about factors that lead to COI arising from pharmaceutical incentivisation. Individuals from regulatory institutions, professional medical associations and health communication/media consultants were deemed policy actors. One of the key objectives of the formative work was to codevelop a multifaceted intervention that could improve GPs’ knowledge, attitude and practices about professional ethics in medical practice. Preliminary analysis of our formative work suggests that in Pakistan professional ethics in medical practice have gradually changed and engaging in pharmaceutical incentivisation has become a norm. Competition in the pharmaceutical market, GPs’ desire to maximise income, combined with weaknesses in health regulation produce a context where an unethical relationship between the pharmaceutical industry and GPs is developed and sustained. Based on our findings, recommendations from the study participants and existing research, a multifaceted intervention has been developed in which, GPs have been invited to seminars to get exposure to messages on medical ethics.

### Intervention

Our intervention is based on multifaceted seminars. As indicated in figure 1, the intervention group has been given seminars on ethics in relation to COI linked with pharmaceutical incentivisation, while the control group has received seminars on clinical issues such as thalassemia and anaemia. The intervention seminars have been developed in four major phases. First, international and national guidelines have been reviewed to develop a brief document on professional ethics in medical practice. The document covers several issues, including pharmaceutical incentivisation in the form of money, other material/nonmaterial benefits and the misuse of the medical license. The document has been endorsed by regulatory bodies at the federal and provincial levels, including the Pakistan Medical Commission (PMC) and the Sindh Healthcare Commission (SHCC). Second, in collaboration with media/communication experts, a filmmaker has been hired to produce an emotive video highlighting the effects of profit-led prescribing on patients’ well-being. Third, GPs have been invited to attend seminars on professional ethics in medical practice and on managing anaemia and thalassaemia in primary care settings. The intervention group GPs has also been sent the PMC-endorsed and SHCC-endorsed brief on ethics in medical practice (reinforcement) and the shortened version of the emotive video (reminder).

**Figure 1 F1:**
[figure not shown]
Diagram of the randomised control trial design. COI, conflict of interest; GP, general practitioner; PMC, Pakistan Medical Commission; ShcC, Sindh Healthcare Commission; SPSR, standardised pharmaceutical sales representative.

The control seminars have been developed in three phases. First, we identify experts in thalassemia and anaemia research and take them on board to teach these topics to the control group GPs. Second, in collaboration with experts, we develop a short educational video on thalassemia and handouts on the management of thalassaemia and anaemia in primary care settings. Third, we invite the control group GPs to attend the seminars.

### Outcome measures

The primary outcome measure of the study is the number of GPs who refuse to take unethical pharmaceutical incentives from the standardised PSRs (SPSRs). The secondary outcomes include GP’s change in knowledge and attitudes about professional ethics in medical practice.

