### Data collection

To measure the impact of the intervention, our data collection is underway, and we anticipate completing it in September/October 2022. We adopt a multimethod approach to collect data on GPs’ knowledge, attitudes and practices in relation to COI linked with pharmaceutical incentivisation. Preintervention and postintervention surveys will be used to assess a change in GPs' knowledge of professional medical ethics and attitudes about engaging in pharmaceutical incentivisation. To collect information about their practices with respect to taking incentives for prescribing, a novel SPSR method will be used, in which trained field researchers will visit the GP clinics as pharmaceutical marketers to assess GPs’ reactions to pharmaceutical incentivisation offers. The SPSRs will recite a script (prepared by the research team) to introduce themselves and the imaginary pharmaceutical company and will market antibiotics commonly prescribed. In this process, the SPSRs make a clear incentivisation offer to GPs for prescribing the medicines and assess whether GPs accept/reject the offer. Since the SPSRs will be representing new pharmaceutical companies and there will be less familiarity between them and GPs, it is anticipated that there can be GPs’ responses, difficult to classify in terms of acceptance or rejection. Therefore, situations in which GPs ignore the SPSR offers or ask them to come back later will be classified as ‘undetermined’. The SPSRs will complete an electronic questionnaire after each GP visit to record information such as GPs’ demographic and clinical characteristics, and their responses to the incentivisation offer. To ensure the data quality, the research team will put several measures in place: recruiting field supervisors who will accompany the SPSRs to GP clinics and ensure the SPSRs’ responses in the questionnaire reflect the interactions with GPs, WhatsApp voice notes to the research team to summarise the interactions and monitoring the SPSR data considering the voice notes as a reference. The questionnaire will be analysed by research team members (also blinded to the allocation of GPs), who will assign a binary outcome for each GP such as ‘refused incentives immediately’, ‘refused incentives after being offered’, ‘asked for and accepted an incentive’, ‘offered and accepted an incentive’, ‘undetermined/undecided’. To prevent the SPSR assessment from being discovered as a simulation that not only can risk the intervention assessment but the SPSRs, in terms of their physical safety, each GP is paid a maximum of two visits. It is also important to note that the SPSRs are blinded to the allocation of GPs.

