### Data analysis

The primary outcome will be assessed by comparing the proportion of GPs classified as ‘yes’ to accepting an unethical benefit (according to the regulator’s guidelines) for prescribing the SPSR’s antibiotic between the control and intervention groups. The proportions will be compared using a two-proportion z-test. Secondary outcomes, such as knowledge and attitude shifts, will be assessed by comparing mean scores in survey responses of control and intervention groups using unpaired t-test and proportions scores in survey responses using the z-test.

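### The primary outcome is defined as refusal in one section and tested as acceptance in another, and the expected undetermined responses make the two non-equivalent

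*Protocol article*

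**What the plan says.** All references are to the protocol article.

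- **Outcome measures** defines the endpoint as a count of refusals: "The primary outcome measure of the study is the number of GPs who refuse to take unethical pharmaceutical incentives".
- **Data analysis** describes the test in terms of acceptance: "The primary outcome will be assessed by comparing the proportion of GPs classified as ‘yes’ to accepting an unethical benefit". The groups are compared with a two-proportion z-test.
- **Data collection** expects some reactions to the standardised pharmaceutical sales representative (SPSR) to fit neither heading: "situations in which GPs ignore the SPSR offers or ask them to come back later will be classified as" undetermined. The same section says the questionnaires go to blinded team members "who will assign a binary outcome for each GP", and then lists five codes: two kinds of refusal, two kinds of acceptance, and undetermined/undecided.
- The paragraph that follows plans 20–25 qualitative interviews to explain the undetermined cases. It does not say how they count in the comparison.
- **Sample size** uses a further wording, the share of GPs supporting pharmaceutical incentivisation, assumed to fall from 80% to 65%.

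**The concern.** Refusal and acceptance are complements only when no third response exists, and this plan expects one. With every assessed GP in the denominator, an undetermined GP falls on the unfavourable side of the refusal endpoint (not a refuser) and on the favourable side of the acceptance endpoint (not an acceptor). The two sections therefore name different primary outcomes.

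The gap matters most if the seminars change the share of undetermined responses. If some GPs in the intervention group put the SPSR off instead of refusing, acceptance falls further than refusal rises. If GPs move from putting the SPSR off to refusing, refusal rises and acceptance does not change. The documents do not say which of these to expect. An author reporting either contrast could point to this article as prespecification, and the choice could be made after the results are known. Blinded coding protects the classification of each visit, but it does not settle which contrast is primary.

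**Working it through.** **1. The plan's own figure.** Inputs from Sample size: 80% v 65%, 80% power, 130 to 135 per group. Alpha is not stated; I assume 0.05 two-sided.

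Unpooled formula: n = (1.960 + 0.842)² × (0.80×0.20 + 0.65×0.35) / 0.15² = 135.2 per group. The pooled formula gives 138. Pooled power is 77.6% at 130 and 79.1% at 135 per group. The stated size is close enough and is not in dispute. It is a calculation for one two-class outcome, without an undetermined class.

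**2. How each code counts, with every assessed GP in the denominator.**

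| Code | Outcome measures (refusal) | Data analysis (acceptance) |
|---|---|---|
| Two refusal codes | event | not an event |
| Two acceptance codes | not an event | event |
| Undetermined | not an event | not an event |

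Write A, R and U for the three shares, with A + R + U = 1. Then the change in R equals minus the change in A, minus the change in U. The two endpoints show the same absolute change only if U changes equally in both arms.

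**3. Size.** Group sizes are 210 intervention and 209 control (Randomisation), and all GPs are taken as assessed. The A/R/U splits are assumptions, because the documents give none. Pooled test: z = (p₁ − p₀) / √[p̄(1 − p̄)(1/210 + 1/209)], where p̄ is the pooled proportion. Acceptance falls 15 points in every row; only its destination differs.

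| Where the fall goes | Control A/R/U % | Intervention A/R/U % | Acceptance | Refusal |
|---|---|---|---|---|
| All to refusal | 70/20/10 | 55/35/10 | −15 points, z = −3.17, p = 0.0015 | +15 points, z = 3.44, p = 0.0006 |
| Half to undetermined | 70/20/10 | 55/27.5/17.5 | −15 points, z = −3.17, p = 0.0015 | +7.5 points, z = 1.80, p = 0.07 |
| All to undetermined | 60/20/20 | 45/20/35 | −15 points, z = −3.07, p = 0.002 | 0 points, z = 0, p = 1.0 |

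Worked line for the second row, refusal: p̄ = (0.275×210 + 0.20×209)/419 = 0.2376; standard error = √[0.2376 × 0.7624 × (1/210 + 1/209)] = 0.0416; z = 0.075/0.0416 = 1.80.

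**4. The divergence can run the other way.** With the numbers that attended (132 control, 135 intervention) and assumed A/R/U counts of 66/26/40 v 67/47/21, acceptance changes by −0.4 points (p = 0.95) and refusal by +15.1 points (p = 0.006).

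**5. What the planned power means for refusal.** Take acceptance falling from 80% to 65% with 132 and 135 GPs. If control has 20% refusal and none undetermined, power for refusal is 79% when the whole fall goes to refusal, 30% when half does and 11% when a quarter does. If control has 10% refusal and 10% undetermined, the first two figures are 90% and 43%. The result depends on a split that the plan does not state.

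**The case against.** The best defence is that the operative text is more coherent than it looks. Data analysis names the test. On a plain reading, a GP who is undetermined is not classified as a yes and stays in the proportion. The promised binary outcome fits a collapse of the five codes into yes and not-yes, and the 80% to 65% assumption runs in the same direction. Outcome measures is then the outlier, and denominator detail is commonly left to an analysis plan that is not shown here.

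That reading is reasonable, and it is why acceptance is the natural candidate. It does not remove the conflict. The section that exists to define the primary outcome says refusal, the collapse is never spelled out, and an analysis plan could follow one section only by contradicting the other.

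Three stronger readings are tempting, and the documents do not support them.

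- *Opposite conclusions.* A reader might infer that the two definitions could be significant in opposite directions. That needs a large imbalance in undetermined responses. In one constructed example (39% v 13% undetermined), acceptance rises 13.8 points, p = 0.024, and refusal rises 13.0 points, p = 0.010. The ordinary risk is positive against null.
- *A third analysis that drops undetermined GPs.* Nothing in the article proposes this.
- *A third endpoint.* The abstract says "The primary outcome measure will be GPs’ prescribing practices". This is a broad label set beside knowledge and attitudes, and Data collection narrows it to taking incentives for prescribing. Whether the label claims too much is a separate question.

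It is also fair to say that the splits are chosen and that nothing in the documents shows the seminars would produce evasion.

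**Conclusion.** The point stands as a contradiction in the current text: two non-equivalent primary outcomes, an expected response class that separates them, and no section that reconciles them. It should be fixed, because it governs the trial's main result.

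Its size cannot be known from the documents. For a 15-point fall in acceptance, the assumed range runs from agreement (all of the fall to refusal), through p = 0.0015 against p = 0.07 (half to undetermined), to p = 0.002 against p = 1.0 (all to undetermined). These figures assume that all 419 GPs are assessed, a pooled z-test is used and the threshold is 0.05 two-sided. If undetermined responses turn out to be rare or equally common in both arms, the two definitions will show nearly the same absolute change.

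**What to change.** Before allocation is linked to outcomes, use one primary definition in Outcome measures, Sample size, Data collection and Data analysis.

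- **Acceptance as primary.** This is the contrast already named in Data analysis and the one closest to the 80% to 65% assumption. Define it as asked-and-accepted or offered-and-accepted versus all other responses, with every assessed GP, including undetermined, in the denominator.
- **Refusal as primary instead.** Change Data analysis to test it, and state in Sample size that the 80% power can be carried over only if the fall in acceptance moves wholly into refusal.

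In either case, name the other contrast as the key secondary and report the distribution of accept, refuse and undetermined by arm. Do not describe a fall in acceptance as a rise in refusal unless the refusal comparison itself supports it. Replace the reference to a binary outcome with the five codes and the stated rule for collapsing them.

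The cost is wording. The five codes are already planned and no new data are needed, but data collection is underway, so the decision should be dated. The downside for the authors is that a fall in acceptance made up only of undetermined responses would have to be reported as such, which is a less favourable conclusion.
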